### Sampling and recruitment

#### HCF.

We will target training all clinical and non-clinical HCF staff who may encounter YGBMSM seeking HPART services at the facility (e.g., nurses, lab staff, guards, receptionists, etc.). The GBMSM+NURSES trainers and peer-led nurses will work closely with facility management to select participants and coordinate training attendance and data collection logistics to minimize service disruption. The training will be held on-site and fitted into the facility activities as done in our previous works. Based on our preliminary analysis of reported numbers from the six facilities, and prior studies, we estimate about 1500 participants across sites. In our earlier studies, 60 to 70% of the staff was trained, but GBMSM+NURSES partners reported incidents of ISD among other staff who were not trained. For the surveys (n=300), we will secure a list of intervention participants from various departments, stratify participants (clinical and non-clinical) and select participants using simple random sampling from each stratum. **For the follow-up** FGDs (n=5), we will use the process and criteria defined in **AIM1**, with 8 to 10 persons per FGD and 20 anti-stigma nurse trainers for the IDIs. **YGBMSM**. We will use a combination of venue-based and snowball sampling to recruit YGBMSM (n=160) per site (totaling 320). Like starfish sampling, this process overcomes the weaknesses of using only venue-based or peer-driven recruitment. The implementing partners will invite known YGBMSM that meets the criteria for the CRT. We will then select initial seeds among the YGBMSM and ask them to invite their peers to the study using coupons. This chain-referral process will continue until we reach the number of participants needed. Based on the referral chains, we will use the seeds and nodes to identify peer groups of 5 to 8. **For the follow-up** FGDs (n=5), we will use the process and criteria defined in **AIM1**, with 8 to 10 persons per FGD and 20 YGBMSM living with HIV for the IDIs.

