**Methodology:**

We will employ the ADAPTT-IT framework to adapt LAFIYA and evaluate its feasibility and effectiveness in addressing intersectional stigma and increasing HPART uptake among YGBMSM residing in Ghanaian slums. In aim 1, we will hold focus groups (n=5) and interviews (n=20) among YGBMSM and two FGDs among GBMSM-led organizations. At the HCF level, we will hold 6 FGDs and interviews (n=20) among nurses. In AIM 2, we will randomly assign 6 healthcare facilities (HCFs) to receive the LAFIYA (n=3) or wait-list control (n=3). Friend groups (cluster) of YGBMSM (N=240) will be assigned to receive LAFIYA (n=120) or a wait-list control (n=120). We will collect 3-, 6-, and 9-months post-intervention data among YGBMSM(n=240) and HCWs(n=300) to measure HPART adherence (primary outcomes), ISD reduction, HIV and status-neutral knowledge (secondary outcomes), and intervention acceptability, appropriateness, and feasibility (implementation outcomes).

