### STEP 8 (Testing/Aim 2): Test the preliminary efficacy of the intervention to address ISD and increase HPART adherence using CRT Design

We will pilot-test the *LAFIYA* multilevel intervention using a clustered randomized control trial (CRT) with 9 months of waitlist control. Our ultimate aim is to adapt the intervention and preliminary test it for future full-efficacy CRT ^118,119^. Although RCT is primarily used in HIV and behavioral interventions, we find CRT better due to our place-based focus and possible sample contamination. In our previous single arm-pilot (2P30MH062294 −20 // Yale #18–001890, PI, [name]), we identified group sleeping arrangements, observed close-knit networks of GBMSM, and the communal nature of slums as contaminants. We will create two pairs of facilities matched by size and location in each city and randomly assign them to receive the LAFIYA-HCF intervention or the control group. Based on friendship networks, we will create GBMSM groups of 5 to 8 members and randomly assign YGBMSM groups to the LAFIYA-YGBMSM intervention or control group. YGBMSM in the intervention group will be matched with intervention HCF for status-neutral services. The YGBMSM in the waitlist control group will be matched with HCFs in the waitlist control for regular testing, PrEP, and care services. Nurses from the intervention HCF will participate as guest facilitators in one of the LAFIYA-GBMSM sessions. They will use that opportunity to contact YGBMSM to visit their facility for status-neutral care. We will collect 3, 6, and 9 months post-intervention data to measure the preliminary efficacy of the intervention and then implement the intervention in the waitlist group after the completion of data collection. We will use 9 months instead of 6 to allow ample time to measure multiple components, **such as viral suppression,** over a sufficient time. **Our primary hypothesis** is that LAFIYA will increase adherence to HPART among YGBMSM participants. **Our secondary hypothesis** is that the multilevel intervention will reduce the ISD that HCF staff convey and YGBMSM experience in HCFs. It will build the HCF’s capacity to implement status neutrality. We will then **conduct a follow-up qualitative study** (FGDs and IDIs) post-intervention among implementers and participants to evaluate their experiences with the intervention and to seek a more profound understanding or explanations for some of the survey findings.

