### Power.

#### YGBMSM:

We perform the power analysis to detect the difference in intervention outcomes using a sample measurement scale (HIV-ASES)^101^ between intervention and control (n=240, control arm=120, intervention arm = 120) by adjusting the Intraclass correlation coefficient (ICC) for the friend group. In a similar setting, a network membership explained 4.08% (i.e., ICC=0.04) of the total variance in outcomes^102^. The ICC of 0.04 and 8 individuals in a friend group will produce the design effect (DE) of 1.28. Approximately 15 peer groups will be randomly assigned to each study arm. A DE of 1.28 and a sample of 240 (120 per arm) will have 92.7% power to detect the medium effect size of 0.50 at a 5% significance level. The medium effect size of 0.50 implies a 5.6 point (SD=11.2) on the outcomes and 0.62 points (SD=1.23) based on standard deviations from HTAS. The sample size of 120 in the intervention group will have 99% and 82% powers to detect the medium and small effect sizes of 0.50 and 0.30, respectively, on the outcome changes within the group. With a 10% attrition rate, 216 participants will have 90% power to detect the medium effect size of 0.50, and 108 participants receiving the intervention will still have 99% for the medium effect size after adjusting for ICC of 0.04.

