#### Criteria:

The person must be between 18 to 25 years old, currently identifies as a cis-gender man, have had sex with another man within 8 months before engaging with the recruitment team, and must reside within a slum in the Accra metropolitan area. **Randomization**. When we complete the recruitment and baseline survey, we will stratify peer groups by the number of peer members and give a group ID to each peer group. Within each stratum with an equal number of peers, we will randomly select groups for intervention using simple random sampling. Thus, we will keep equal samples and peer groups between the two study arms.

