#### Randomization.

We will assign 3 HCFs to intervention or control groups based on size; we will first stratify 6 HCFs into groups of two, larger, medium, and smaller sizes, and assign one from each stratum to either arm using SRS.

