#### Data analysis.

We will use the intent-to-treat (ITT) technique to analyze data. We considered other methods (e.g., per protocol approach), but ITT is less biased since all participants are assessed whether they received the intervention or not. Data collected will be exported to Stata for cleaning and further analysis. Using the Monte Carlo Markov Chain approach based on a multivariate normal distribution of items, we will assess missing patterns in the instrument and impute missing responses with at least 70% of responses. Instruments scores will be calculated with observed and imputed responses. We will summarize the characteristics of participants and calculate Cronbach’s alpha to check internal reliability within scales. We will calculate a mean with a confidence interval for the variables and proportions of responses to the primary and secondary outcome variables. Variables with skewed distribution will be considered for being log-transformed or categorized in ordinal form. We will run inferential statistics such as paired t-test to compare pre-and post-means, McNamara’s test to compare pre-and post-proportions, and correlation analysis to examine the relationship between variables. We will also develop longitudinal models of the outcomes repeatedly measured at baseline, 3, 6, and 9 months post-intervention using a generalized linear mixed effect model (GLMM) with random intercept and peer group, which incorporate ICCs. The GLMM will include time-group interaction to estimate the intervention effect and pre-post changes. The GLMM will consist of all completed observations and drop-outs observed at least once post-intervention. Thus, we will not miss any individuals unless they are entirely missing at all post-intervention periods. Residuals will be assessed for normality assumption and influential outliers diagnosed with leverage, Cook’s distance, and DFFIT. The GLMM will be replaced with logistic and Poisson regressions with random effects when an outcome is binary and count data. We will repeat the same models separately for each site and compare the effect sizes between the sites. When we find any demographics, which are not equivalent between the two interventions, they will be included in the model as covariates. Acceptability, feasibility, and appropriateness will be evaluated with descriptive statistics of the implementation outcomes. **The process defined in AIM**1 will be used to analyze the follow-up qualitative data.

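### The YGBMSM recruitment target of 320 contradicts the powered sample of 240; the two facility-pairing schemes disagree, and the per-site analysis has no defined sites

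*Protocol article*

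**What the plan says.** **Sample size.** The abstract (Methodology) states "Friend groups (cluster) of YGBMSM (N=240) will be assigned to receive LAFIYA (n=120) or a wait-list control (n=120". The Power section for YGBMSM uses the same figures, "n=240, control arm=120, intervention arm = 120", with about 15 peer groups per arm. Under Step 8, Sampling and recruitment, the plan is "to recruit YGBMSM (n=160) per site (totaling 320", which implies two sites.

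**Facilities.** The Step 8 overview says "We will create two pairs of facilities matched by size and location in each city". The HCF Randomization section says "we will first stratify 6 HCFs into groups of two, larger, medium, and smaller sizes", with one facility of each stratum going to each arm. The abstract and the HCF power paragraph also have six facilities.

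**Sites.** Study setting names Accra as the study area, and a YGBMSM participant "must reside within a slum in the Accra metropolitan area". The Data analysis section for Aim 2 nevertheless says "We will repeat the same models separately for each site and compare the effect sizes between the sites". No second city is named. The word site is used for the facilities and for recruitment in the same Sampling and recruitment paragraph, and for survey locations under Data collection.

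**The concern.** Sample size and facility randomisation have to be settled before the first participant is enrolled, so a later analysis plan cannot repair them. Chain referral runs until the required number is reached, which makes that number the stopping rule, and the protocol gives two. Recruiting 320 takes 80 more people from a hidden, stigmatised population than the power section justifies. Stopping at 240 departs from the recruitment section. Either way, the final N could later be questioned as a choice made after the fact.

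The two facility schemes differ in the number of facilities and in whether location is a matching factor. The per-site comparison is a stated analysis whose unit is undefined, and whether it can be estimated at all depends on which meaning is chosen.

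**Working it through.** **Inputs (Power section, YGBMSM).** The ICC comes from a cited study in a similar setting, where "a network membership explained 4.08% (i.e., ICC=0.04) of the total variance in outcomes". Group size is 8, the standardised effect is 0.50, and significance is 5%. Sidedness is not stated; two-sided is assumed because it reproduces the plan's figure.

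**Formulas.** Design effect DE = 1 + (m − 1) × ICC = 1 + 7 × 0.04 = 1.28. Effective n per arm = n / DE. Power ≈ Φ(d × √(n_eff / 2) − 1.96). A noncentral-t version is given where it differs.

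**Reproducing the plan**
- 240: 120 / 1.28 = 93.75 per arm. 0.5 × √46.875 − 1.96 = 1.463, so power is 92.8% (t: 92.6%). Stated: 92.7%.
- 216, after 10% attrition: 108 / 1.28 = 84.4 per arm. Power is 90.1% (t: 89.8%). Stated: 90%.
- Groups per arm: 120 / 8 = 15, as stated.

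The power section is therefore internally coherent and belongs to 240.

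**The same calculation at 320**
- 160 / 1.28 = 125 per arm. 0.5 × √62.5 − 1.96 = 1.993, so power is 97.7% (t: 97.6%).
- After 10% attrition (288): 144 / 1.28 = 112.5 per arm, so power is 96.3%.
- Groups of 8 per arm: 160 / 8 = 20, against the stated 15.

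**Does attrition explain 320?** 240 / 0.90 = 266.7, so 267. Reaching 320 needs a loss of 1 − 240 / 320 = 25%. The plan states 10% and applies it downward, from 240 to 216.

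**Facility count.** Two pairs are 4 facilities: 4 in one city, 8 in two. Neither is 6. Three size strata of two give 3 × 2 = 6, which agrees with the abstract and the HCF power paragraph.

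**What site could mean in the per-site models**

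| Meaning | Number in the plan | Between-arm effect within a site? |
|---|---|---|
| City | 1 (Accra) | Yes, but no other site to compare with |
| Facility | 6 | No: each facility is in one arm, and YGBMSM are matched to facilities of their own arm |
| Recruitment area within Accra | 2, from 320 / 160, but not defined | Yes, if each area contains both arms |

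Under the third meaning, with equal arms in each site, power within one site at effect 0.50 is:
- 120 per site: 60 / 1.28 = 46.9 per arm, 68%.
- 160 per site: 80 / 1.28 = 62.5 per arm, 80%.

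The comparison between sites is weaker still. Each half-sample effect has twice the variance of the overall effect, so their difference has four times that variance and twice the standard error.

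**The case against.** The strongest defence is that little numerical harm follows. Power is above 90% at either total before attrition and about 90% or more after it. The trial is a pilot for preliminary efficacy, and its main analysis is one pooled mixed model that does not depend on how site is defined. The dedicated facility randomisation section is clear and agrees with the abstract, so the conflicting sentence sits in an overview. All of this stands, and it limits the point to contradiction.

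Four stronger readings are tempting, and the protocol does not support them.
- A reader might infer that 80 recruits would have no place in the allocation. The YGBMSM Randomization section allocates peer groups after recruitment is complete, within group-size strata, and fixes no total. All 320 would be randomised.
- A reader might infer that the per-site models can never be run because no facility contains both arms. But 160 per site totalling 320 means two sites, not six facilities. Peer groups, not places, are randomised, so two areas within Accra could each hold both arms.
- A reader might infer a two-city trial. The overview gives no number of cities and names no second one.
- A reader might infer that the trial is underpowered. The larger total would only raise power.

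The defence does not remove the conflict over N or over facility pairing. The two areas that would rescue the per-site comparison are not defined, and peer-group randomisation is stratified by group size only.

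**Conclusion.** The contradiction holds. The recruitment target exceeds the powered sample by 80 people (80 / 240 = 33%), and the stated attrition accounts for only 27 of them. The stated 92.7% belongs to 240; 320 would give about 97.6% on the same ICC, group size and effect, assuming a two-sided test. The facility pairing in the overview yields 4 or 8 facilities and cannot produce the 6 used elsewhere. The per-site comparison is undefined as written. It becomes estimable only if two areas within Accra are specified and each contains both arms, and even then each site has about 68% or 80% power for an effect of 0.50.

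This warrants correction before recruitment because it concerns the enrolment target and the randomisation structure. It does not show that the planned power is inadequate. The protocol does not show which total is intended, though 240 is the one its power calculation supports.

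**What to change.** 1. State one YGBMSM total in the abstract, Sampling and recruitment, and Power. If it is 240, change the recruitment figure. If it is 320, restate the abstract and the power section: 160 per arm, 20 groups of 8 per arm, about 97.6% power, and 96.3% after 10% attrition.
2. Replace the facility-pairing sentence in the Step 8 overview with the scheme in the HCF Randomization section: six facilities, three size pairs, one of each pair per arm. If location matching is wanted, add it there.
3. Either delete the per-site models and the between-site comparison, or define two sites within Accra, stratify peer-group randomisation by site as well as group size, and label the comparison exploratory with its per-site power.

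Items 1 and 2 cost only wording while recruitment has not begun, as Trial Status reports; choosing 320 also means enrolling and following 80 people beyond the powered sample. Keeping the per-site models adds a stratification factor. With group sizes of 5 to 8 and two sites there are up to 4 × 2 = 8 strata. 240 people form 30 to 48 groups, so about 4 to 6 groups per stratum on average. That is workable, but strata with an odd number of groups will not split evenly.

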### Power.

#### YGBMSM:

We perform the power analysis to detect the difference in intervention outcomes using a sample measurement scale (HIV-ASES)^101^ between intervention and control (n=240, control arm=120, intervention arm = 120) by adjusting the Intraclass correlation coefficient (ICC) for the friend group. In a similar setting, a network membership explained 4.08% (i.e., ICC=0.04) of the total variance in outcomes^102^. The ICC of 0.04 and 8 individuals in a friend group will produce the design effect (DE) of 1.28. Approximately 15 peer groups will be randomly assigned to each study arm. A DE of 1.28 and a sample of 240 (120 per arm) will have 92.7% power to detect the medium effect size of 0.50 at a 5% significance level. The medium effect size of 0.50 implies a 5.6 point (SD=11.2) on the outcomes and 0.62 points (SD=1.23) based on standard deviations from HTAS. The sample size of 120 in the intervention group will have 99% and 82% powers to detect the medium and small effect sizes of 0.50 and 0.30, respectively, on the outcome changes within the group. With a 10% attrition rate, 216 participants will have 90% power to detect the medium effect size of 0.50, and 108 participants receiving the intervention will still have 99% for the medium effect size after adjusting for ICC of 0.04.

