## Introduction

In Ghana, the HIV epidemic continues to pose significant public health challenges, particularly among gay, bisexual, and other men who have sex with men (GBMSM)^1–13^. Contributing to less than 2% of Ghana’s population, the HIV prevalence of this key population surpasses the national average by more than eightfold, emphasizing the need for targeted interventions to improve early detection, care linkage, and reduce community transmission^14–16^. Young GBMSM (YGBMSM) represent a vulnerable population that requires focused attention due to their increased HIV vulnerability^17–20^. YGBMSM aged 18 to 24 years comprise a sub-risk population within the broader GBMSM community, accounting for 63% of known HIV cases among GBMSM in Ghana^15^.

In addition to being young or GBMSM, living in urban areas, especially slums, can increase HIV vulnerability^21–23^. Slums house over 30% of Ghana’s urban residents, about 40% of our study area (Accra)^24,25^, and GBMSM in Accra have the highest HIV prevalence (44%) compared to nationwide GBMSM (18%)^26^. YGBMSM in slums remain at heightened vulnerability as slums remain documented high HIV-burdened areas due to structural issues (e.g., lack of access to care) and behavioral factors (e.g., transactional sex)^21–5,21,27–37^.

The advent of HIV self-testing (HIVST) and Pre-Exposure Prophylaxis (PrEP) alongside the established Antiretroviral Therapy (ART) represents significant milestones in the ongoing efforts to curb HIV incidence and enhance treatment adherence among diverse populations, including GBMSM^38–40^. HIVST facilitates repeated testing of self, partners, and clients^38^. The World Health Organization (WHO) recommends oral PrEP for persons with seronegative HIV tests at substantial and ongoing vulnerability to HIV. PrEP effectively prevents HIV acquisition but requires high adherence; adherence is the main predictor of effectiveness^39,40^. Studies in Ghana have reported low levels of knowledge but high acceptability of PrEP and HIVST among GBMSM^41–43^. Perspectives of policymakers in Ghana also indicate that HIVST is highly acceptable, but national guidelines and stakeholder consultations are necessary for successful implementation^44^.

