### Measures.

#### Demography, HIV testing, and ISD descriptive variables.

We will assess important baseline characteristics for describing the sample, including age, income, gender, education, ethnicity, relationship status, religion, sexual orientation, sexual behavior, HIV knowledge, HIV testing, PrEP and ART readiness, and history. Experiences of ISDs, access, and utilization of health and social services, civic engagement, and neighborhood. **Primary outcomes:** At baseline, 3, 6, and 9 months, we will measure the preliminary efficacy of LAFIYA. We will measure knowledge of HIV and HPART; and willingness to adhere to HPART pre and post-intervention. HPART adherence characteristics (rates, time, mode, location) and biomarkers (Table 2). **Secondary outcomes:** For ISD reduction, we will measure internalized and interpersonal level ISD at baseline and post-intervention surveys among YGBMSM. We will measure HCF-level ISD to understand participant experiences at baseline and changes in HCW stigmatizing beliefs and practices (Table 2). **Implementation outcomes:** We will measure acceptability, appropriateness, and feasibility using expanded Proctors validated measures at pre-immediate and post-intervention surveys at all levels (Table 2)^103^.

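### The 92.7% power covers a scale score in all 240 men, not PrEP or ART adherence, and the article is inconsistent on whether knowledge is a primary outcome

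*Protocol article*

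**What the plan says.** **Power.** The YGBMSM part of the Power section starts from one instrument: "We perform the power analysis to detect the difference in intervention outcomes using a sample measurement scale (HIV-ASES"), with "n=240, control arm=120, intervention arm = 120". It uses an ICC of 0.04 and friend groups of 8, giving a design effect (DE) of 1.28, and concludes: "A DE of 1.28 and a sample of 240 (120 per arm) will have 92.7% power to detect the medium effect size of 0.50". The test level is 5%. After 10% attrition (216 men) it states 90%. The 0.50 is translated into points on continuous scales (5.6 with SD 11.2; 0.62 with SD 1.23).

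**Primary hypothesis.** STEP 8 (Testing/Aim 2) says that the primary hypothesis "is that LAFIYA will increase adherence to HPART among YGBMSM participants". HPART is the article's term for HIV testing, PrEP and ART. The same section gives viral suppression as a reason for following participants to 9 months.

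**Population.** The Criteria for the trial cover age, gender, sex with a man and residence, and set no HIV-status condition. The Introduction notes that the WHO "recommends oral PrEP for persons with seronegative HIV tests". It gives HIV prevalence among GBMSM as 44% in Accra and 18% nationally.

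**Outcome list.** The Abstract names HPART adherence as primary and classes "HIV and status-neutral knowledge (secondary outcomes") as secondary. The Study design overview also names HPART adherence as primary. Measures, under its primary outcomes label, says: "We will measure knowledge of HIV and HPART; and willingness to adhere to HPART pre and post-intervention", and then adds adherence characteristics and biomarkers.

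**The concern.** The power figure and the primary hypothesis refer to different quantities in different populations. A scale score can be collected from every man. Adherence to PrEP is defined only for men without HIV, and adherence to ART or viral suppression only for men with HIV. With mixed enrolment, each of these two components draws on a fraction of the 120 per arm. The only between-arm power the section gives assumes all 120.

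The section on HCF power then says the sample sizes are expected to suffice for medium effects. A reader would take 92.7% as the trial's power for its primary outcome, and could later read a null ART or PrEP result as evidence of no effect when the comparison was never that sensitive.

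The outcome list adds to this. If knowledge and willingness count as primary, an improvement in either could be reported as meeting the primary outcome even though adherence did not change. Under the Abstract's classification it could not.

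**Working it through.** **Inputs.** From the Power section: 120 per arm, effect size d = 0.50, ICC 0.04, group size 8, 5% level (taken as two-sided, which reproduces the stated figure), 10% attrition. From the Introduction: HIV prevalence 18% and 44%. Applying these to the sample is an assumption.

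**Step 1: the stated figure.** DE = 1 + (8 − 1) × 0.04 = 1.28. Effective n per arm = 120 / 1.28 = 93.75. A two-sided two-sample t test with d = 0.50 (noncentral t) has power 92.6%; the normal approximation gives 92.8%. With 108 per arm, 108 / 1.28 = 84.4 and power is 89.8% (normal approximation 90.1%), against the stated 90%. The arithmetic is right for a score seen in all 240.

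**Step 2: component populations.** With prevalence p, ART adherence has 120 × p men per arm and PrEP adherence 120 × (1 − p). If HIV status is spread evenly over friend groups, the cluster size falls to 8 × share and DE = 1 + (8 × share − 1) × 0.04.

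| Component | Prevalence | n per arm | DE | Effective n | Power | Power with DE kept at 1.28 |
|---|---|---|---|---|---|---|
| ART | 18% | 21.6 | 1.02 | 21.2 | 36% | 29% |
| ART | 44% | 52.8 | 1.10 | 48.0 | 68% | 61% |
| PrEP | 18% | 98.4 | 1.22 | 80.5 | 88% | 87% |
| PrEP | 44% | 67.2 | 1.14 | 59.0 | 77% | 72% |

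The last column is the less favourable case. If HIV status clusters within friend groups, the truth moves towards it.

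**Step 3: 10% attrition.** With the reduced cluster size, ART power is 33% (18% prevalence) to 64% (44%), and PrEP power is 86% (18%) to 73% (44%). With DE kept at 1.28, the figures are 26–57% for ART and 67–83% for PrEP.

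**Step 4: HIV testing.** Nothing in the article confines testing to one of these two subgroups, so no such reduction applies.

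**Step 5: the outcome list.**
- Abstract: HPART adherence primary, knowledge secondary.
- Study design overview: HPART adherence primary.
- STEP 8: primary hypothesis on HPART adherence.
- Measures: knowledge and willingness under primary outcomes, alongside adherence characteristics and biomarkers.

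Three places agree, and Measures departs from them.

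**The case against.** **It is a pilot.** The trial tests preliminary efficacy and is meant to inform a later full trial, so low power in a subgroup limits interpretation without invalidating the study. This stands and lowers the severity. It does not excuse a specific power claim that covers something other than the primary outcome.

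**The scale is only an example.** The section calls HIV-ASES a sample scale and claims no power for PrEP or ART separately. This also stands: the fault is that the figure's scope is not stated, not that a component figure is wrong.

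**A table or analysis plan may settle it.** Measures refers to a Table 2 that is not shown, and detailed endpoint definitions may sit elsewhere. Neither would change the basis of the 92.7% or remove the disagreement between the Abstract and Measures.

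**More men may be recruited.** Sampling and recruitment mentions 320. With 160 per arm and the Step 2 method, ART power would be 46% (160 × 0.18 = 28.8 per arm) to 80% (160 × 0.44 = 70.4), and PrEP power 88% to 95%. But the Abstract and the Power section both use 240.

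**Proportions are not in themselves the problem.** In all 240 with DE 1.28, an assumed 50% against 70% has about 80% power, and 50% against 74% about 93%. The loss shown here comes from the smaller populations. How a binary outcome fares in all 240 depends on a difference the article does not specify.

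**Stronger readings.** A reader might infer that type I error is inflated across many primary tests and visits. The article does not list a countable set of tests, and Data analysis plans a longitudinal mixed model for the repeated outcomes, so no error rate can be derived. A reader might also infer that adherence will be compared only among men who start PrEP or ART. Data analysis commits to intention to treat and proposes no such comparison.

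**Conclusion.** The point holds as a mismatch of scope and a contradiction in the outcome list. It is not an arithmetic error.

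- The stated 92.7%, and 90% after attrition, apply only to a continuous score observed in all 240 men.
- At d = 0.50, power is about 36–68% for ART adherence and 77–88% for PrEP adherence, or 29–61% and 72–87% if the design effect stays at 1.28. Attrition of 10% takes off a few points more.
- These ranges assume a sample prevalence between 18% and 44%, figures that describe GBMSM not restricted to ages 18 to 25. They also assume the same ICC in each subgroup and that every man of the relevant status contributes.

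It would be too strong to say that every primary component is underpowered. PrEP stays above 80% at 18% prevalence, and testing does not lose its denominator. The serious shortfall is in ART.

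On the outcome list, Measures conflicts with the Abstract and does not match the Study design overview or STEP 8. This should be fixed, but for a preliminary-efficacy pilot it is not a fatal flaw.

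**What to change.** 1. In the Power section, say that the 92.7% and 90% refer to a scale score observed in all 240 men.
2. Add power for PrEP adherence in HIV-negative men and ART adherence in HIV-positive men, over 18% to 44% prevalence and with the design-effect assumption stated. Where the outcome is a rate, express it as a difference in proportions.
3. Reconcile the Abstract, Study design overview and Measures so that HPART adherence alone is primary, with knowledge and willingness secondary.

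One way to keep all 240 men in the primary comparison is a single status-appropriate endpoint at 9 months in everyone randomised. It is not the only way. It would require HIV status for every man and a decision on how to count HIV-negative men who are not on PrEP, which is debatable because the Introduction ties PrEP to substantial and continuing risk.

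The cost of steps 1 to 3 is wording and a recalculation, with no extra participants; recruitment had not begun when the article was written. The downside is a less favourable stated power for the ART and PrEP components.
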